Subgroup analysis as per Gestational Age (divided using the cut-offs defined in the minimisation procedure: < 32 Weeks, 32 - 37 weeks, > 37 Weeks) and Sex (Male and Female). The analysis has been performed through fitting a linear model adjusting for baseline and minimisation factors and fitting an interaction term between treatment allocation and the variable being subsetted (gestational age and sex in two separate analyses). Complete case analyses have been performed and the numbers in each subgroup from the complete case population are reported in the forest plot in eFigure 4. Subgroup analysis looking at subgroups on BMI, Glucose Level, Arterial Stiffness and Left Ventricular Mass (from MRI sub-study). The cut-offs have been determined through taking the ceiling of the median at baseline for each variable with the exception of Glucose; as this variable has a much smaller range the cut off is the median rounded to one decimal place. A complete cases analysis has been performed and the numbers in each subgroup is reported. Post-hoc exploratory sub-group analysis was also performed to understand whether there was difference in effect related to volume of supervised or unsupervised exercise sessions completed (above or below 3 hours per week) presented in eTable 4.

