**4. FIGURES**

eFigure 1. Adjusted mean difference in systolic blood pressure according to level of blood pressure imputed for missing values in the intervention and control arms. From left to right imputed values increase in the intervention arm and reduce in the control arm. Imputed values are based on levels expected in each quantile of the study population. Change is presented as adjusted mean difference in systolic blood pressure after 16 weeks moderate to high intensity exercise in mmHg with 95% confidence interval error bars

[figure not shown]

eFigure 2. Adjusted mean difference in diastolic blood pressure after 16 weeks moderate to high intensity exercise according to level of blood pressure imputed for missing values in the intervention and control arms. From left to right imputed values increase in the intervention arm and reduce in the control arm. Imputed values are based on levels expected in each quantile of the study population. Change is presented as adjusted mean difference in diastolic blood pressure after 16 weeks moderate to high intensity exercise in mmHg with 95% confidence interval error bars

[figure not shown]

eFigure3. Sensitivity analysis using Multiple Imputation by Chained Equations (MICE) on the primary outcomes of 24hour awake ambulatory diastolic and systolic blood pressure. Change is presented as adjusted mean difference in each blood pressure variable between intervention and control groups after 16 weeks moderate to high intensity exercise in mmHg with 95% confidence interval error bars

[figure not shown]

eFigure 4. Forest plots to demonstrate the adjusted mean difference in awake systolic ambulatory blood pressure (Panel A) and awake ambulatory diastolic blood pressure (Panel B) after a 16 week moderate to high intensity exercise intervention compared to a control group according to different subgroups of the study population. Subgroups are based on defined values of baseline body mass index, glucose level, arterial stiffness and left ventricular mass (for those who underwent magnetic resonance imaging) Change is reported as the adjusted mean difference in mmHg with errors bars representing 95% confidence intervals. Abbreviations: BMI = body mass index, LV = left ventricular, SBP = systolic blood pressure, DBP = diastolic blood pressure.

PANEL A. Awake Systolic Ambulatory Blood Pressure

[figure not shown]

PANEL B. Awake Diastolic Ambulatory Blood Pressure

**
[figure not shown]
**

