| 16 Weeks | 43 | 127.7 (12.6) | | 84 | 125.8 (10.0) | -0.1 (-3.5,3.3) | | | |
| 52 Weeks | 35 | 129.2 (11.8) | | 69 | 125.5 (11.8) | 1.8 (-1.9,5.6) | | | |
| **Weekly Exercise Supervised < 3 hours** | | | | | | | | | |
| Baseline | 57 | | 128.8 (9.6) | 101 | 128.3 (8.7) | |  | | |
| 16 Weeks | 33 | | 125.9 (10) | 84 | 125.8 (10.0) | | 0.3 (-3.5, 4.1) | | |
| 52 Weeks | 33 | | 126.3 (14.8) | 69 | 125.5 (11.82) | | 1.3 (-2.7, 5.6) | | |
| **24 Hour Awake Ambulatory Diastolic Blood Pressure** | | | | | | | | | |
| **Weekly Exercise Supervision ≥ 3 hours** | | | | | | | | | |
| Baseline | 45 | | 77.4 (6) | 101 | 77.4 (7.5) | |  | | |
| 16 Weeks | 43 | | 77 (6.8) | 84 | 75.5 (6.7) | | 0.9 (-1.4,3.3) | | |
| 52 Weeks | 35 | | 78.3 (8.0) | 69 | 75.2 (7.8) | | 2.3 (-0.4,4.9) | | |
| **Weekly Exercise Supervision < 3 hours** | | | | | | | | | |
| Baseline | 57 | | 76.7 (6.7) | 101 | 77.4 (7.5) | |  | | |
| 16 Weeks | 33 | | 75.7 (7.2) | 84 | 75.5 (6.7) | | 0.3 (-2.4, 3.0) | | |
| 52 Weeks | 33 | | 75.2 (8.4) | 69 | 75.2 (7.8) | | 0.2 (-2.6, 4.9) | | |
|  |  | |  |  |  | |  | | |
| **Oxygen Uptake Peak** | | | | | | | | | |
| **Weekly Exercise Supervision ≥ 3 hours** | | | | | | | | | |
| Baseline | 45 | | 34.1 (7.8) | 100 | 34.7 (7.4) | |  | | |
| 16 Weeks | 45 | | 36.7 (7.6) | 92 | 34.6 (6.7) | | 3.0 (1.5, 4.5) | | |
| 52 Weeks | 41 | | 35.2 (8.3) | 81 | 34.5 (7.3) | | 0.7 (-0.9, 2.2) | | |
| **Weekly Exercise Supervision < 3 hours** | | | | | | | | | |
| Baseline | 56 | | 32.2 (6.6) | 100 | 34.7 (7.4) | |  | | |
| 16 Weeks | 39 | | 35.9 (6.2) | 92 | 34.6 (6.7) | | 2.4 (0.8, 3.9) | | |
| 52 Weeks | 36 | | 32.5 (6.2) | 81 | 34.5 (7.3) | | -0.6 (-2.2, 2.2) | | |
|  | | | | | | | |  | |

1. Protocol

**Study Title:**  Trial of Exercise to Prevent Hypertension in young Adults

**Internal Reference Number / Short title:** TEPHRA

**Ethics Ref:** 16/SC/0016 **IRAS Ref:** 194729

**Date and Version No:** 10th December 2020, Version 3.1

| **Chief Investigator:** | [name], PhD, FRCP  Professor of Cardiovascular Medicine and Consultant Cardiologist  Oxford Cardiovascular Clinical Research Facility  University of Oxford  Email: [contact]  [contact]  [contact] |
| --- | --- |

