## Analysis of Outcome Measures

Descriptive statistics (mean, standard deviation, standard error, range, etc) will be calculated for each outcome for each group. Differences in the primary and secondary outcomes will be compared between intervention and control groups.

Mean changes in blood pressures and cardiovascular fitness will be compared across the population and correlated with cardiovascular endpoints including cardiac structure and function reported from cardiac MRI and echocardiogram.

Demographic and physiological characteristics of the participants will be added to regression models as covariates to explore the determinants of change in blood pressure comparing preterm and full term born participants.

Statistical analysis will be carried out using a computer software package, applying statistical methods to analyse dependent and independent variables within the study database. The variable will be plotted to categorize distribution and assess if the data is normally distributed which will guide the statistical methods. Methods such as the Student T-test will assess for differences between the groups and linear regression analysis will be used to assess if the study variables can explain differences in primary outcome. It is hoped that this will then allow for clear understanding on how the cardiovascular system adapts following exercise training and how remodelling may differ according to birth history and early life exposures. For the sub-study, the statistical analysis will be carried out using a computer software package and data will be analysed using paired and independent t-test. This will access the variability of circulating blood biomarkers within the same participant across both visits and also between each participant.

A detailed statistical analysis plan will be written with our statistical team and will be completed before receipt of the data.

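### Four continuous modifiers (BMI, glucose, arterial stiffness, LV mass) are cut at or near the baseline median and shown only as subgroups, with no continuous treatment-by-modifier interaction stated

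*Supplement*

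**What the plan says.** Section 3 of the Supplement (Subgroup Analysis) describes two sets of subgroups that concern this point. For gestational age and sex it describes a linear model adjusted for baseline and the minimisation factors, "fitting an interaction term between treatment allocation and the variable being subsetted (gestational age and sex in two separate analyses". For BMI, glucose, arterial stiffness and LV mass it gives the rule for the cut: "The cut-offs have been determined through taking the ceiling of the median at baseline for each variable". Glucose is the exception because of its narrow range; there, "the cut off is the median rounded to one decimal place". The analysis is on complete cases.

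The legend of eFigure 4 shows how the four variables are reported: "Subgroups are based on defined values of baseline body mass index, glucose level, arterial stiffness and left ventricular mass", with an adjusted mean difference and 95% CI for each subgroup, in one panel for systolic and one for diastolic pressure.

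In the protocol, section 11.3 (Analysis of Outcome Measures) says that participant characteristics "will be added to regression models as covariates to explore the determinants of change in blood pressure". It also refers to a detailed statistical analysis plan, which is not among the documents shown.

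**The concern.** Each of the four variables is continuous. Splitting it in two treats people just either side of the cut as different and everyone within a half as alike. Any gradient of treatment effect inside a half is lost.

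This matters because the protocol's Trial Rationale names the poorly explained heterogeneity of blood pressure response as a reason for the trial. The sample was sized for a main effect of 5 mmHg, so precision for effect modification is limited from the start. The overall result is null, so readers will look to eFigure 4 for anyone who might benefit. As described, they can only compare pairs of intervals by eye. No estimate says how the treatment effect changes with the modifier.

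The covariate analysis in protocol section 11.3 does not fill the gap. A covariate main effect describes how the characteristic relates to blood pressure, not how it changes the effect of exercise.

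**Working it through.** The documents state no information-loss or subgroup-power figure, so there is none to reproduce.

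**Inputs**
- Cut rule: ceiling of the baseline median (BMI, arterial stiffness, LV mass) or median rounded to one decimal (glucose); Supplement section 3.
- Participants with 16-week systolic pressure: 43 + 33 in the exercise arm and 84 controls, so 160; eTable 4.
- Distribution of the modifiers and shape of the effect modification: not given, so assumed, with a range below.

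**Formula.** For a linear interaction, the share of information kept by a split is the squared correlation between the modifier X and the indicator X > c. For a standard normal X this is φ(c)² / [Φ(c)(1 − Φ(c))].

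**Cut exactly at the median (c = 0).** 0.3989² / (0.5 × 0.5) = 2/π = 0.637, so 36.3% is lost. Then 160 × 0.637 = 102, and 1/0.637 = 1.57 times as many people would be needed for the same precision.

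**Cut above the median.** A ceiling can only move the cut upwards. How far, in SD units, depends on the SD of each variable, which is not given. For a normal modifier:

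| Cut above median | Share in lower group | Loss |
|---|---|---|
| 0.1 SD | 54.0% | 36.6% |
| 0.25 SD | 59.9% | 37.8% |
| 0.5 SD | 69.1% | 41.9% |
| 0.75 SD | 77.3% | 48.3% |
| 1 SD | 84.1% | 56.1% |

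**Other shapes, exact median cut.** Uniform 25%; lognormal (log-SD 0.15) 37.5%; gamma (shape 4) 41%; lognormal (log-SD 0.5) 48%; Laplace 50%.

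**Step-shaped modification.** If the treatment effect jumps exactly at the cut and is flat elsewhere, the split loses nothing. With a normal modifier and a jump at the median, a linear term would then lose 36%.

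**Effect on power.** Take an interaction that would have 80% power if tested on the continuous scale. After an exact median split the power is Φ(2.8016 × √(2/π) − 1.96) = Φ(0.275) = 61%. A simulation with N = 160, a normal modifier and a linear interaction gave 78% continuous, 58% with a median split and 54% with a cut 0.5 SD above the median.

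**The case against.** The strongest reply has four parts.

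1. *These are supportive displays, and no test on them is described.* This stands. An interaction term is written out only for gestational age and sex. A reader might infer that low-powered interaction tests were run on the four split variables, but the text does not say so. The point is that no interaction estimate is stated for them, not that a stated test was weakened.

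2. *The 36% cannot be read as a known loss.* This also stands. It needs normality, a linear effect and a cut exactly at the median. The documents establish none of these, and the stated rule places the cut at a ceiling or a rounded value. Hence the range.

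3. *The cut-offs are fixed numbers taken from baseline, not chosen on outcome.* Correct. A reader might infer that the cut-offs cannot be used in other data, or that false positives are inflated. Neither follows: a rounded value can be applied anywhere, and nothing suggests that it was tuned to the result. It does remain a feature of this sample and not an established threshold.

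4. *The protocol's main heterogeneity question is birth history, which has its own interaction model, and the separate analysis plan may have specified more.* The first half lowers the weight of the point. On the second, the plan is not shown, so nothing is claimed about it. The analysis that the Supplement reports as done is the split one.

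**Conclusion.** The point holds as a minor improvement to the exploratory analysis. Four continuous modifiers are reduced to two groups each at or near the sample median, and no estimate of how the treatment effect varies with them is stated. The loss is about 36% for a normal modifier, a linear effect and an exact median cut, and more when the ceiling lifts the cut. Across the shapes and positions tried it is about 25% to 56%, and nil for a step at the cut. Nothing in the documents argues for a step at a rounded sample median.

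The equivalent of 102 out of 160 applies to systolic pressure under the normal, linear assumption. The 160 is an upper bound, since the baseline modifier must also be present. A reader might want the same figure for LV mass from the planned 100 MRI participants. The documents shown give no complete-case count for that group, and planned enrolment should not be set beside an analysed count, so none is offered.

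It would also be wrong to infer any doubt about the main result, which does not use these splits.

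**What to change.** For 16-week systolic and diastolic pressure, take the adjusted linear model that section 3 already uses and add an interaction between treatment and the continuous baseline value of each variable, one at a time: BMI, glucose, arterial stiffness and LV mass. Report the slope (change in treatment effect per unit of the modifier) with its 95% CI and the number analysed. Check linearity with a spline. Label the results exploratory, since they would be added with the main result known. Keep eFigure 4 for display, and give for each variable the cut-off used and the baseline median and SD, so that readers can see how far the ceiling moved the cut.

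Cost: 4 variables × 2 outcomes = 8 fits, plus up to 8 spline checks, on data already in hand. The price is an assumption of a smooth, roughly linear interaction, which the spline is there to examine.

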**4. FIGURES**

eFigure 1. Adjusted mean difference in systolic blood pressure according to level of blood pressure imputed for missing values in the intervention and control arms. From left to right imputed values increase in the intervention arm and reduce in the control arm. Imputed values are based on levels expected in each quantile of the study population. Change is presented as adjusted mean difference in systolic blood pressure after 16 weeks moderate to high intensity exercise in mmHg with 95% confidence interval error bars

[figure not shown]

eFigure 2. Adjusted mean difference in diastolic blood pressure after 16 weeks moderate to high intensity exercise according to level of blood pressure imputed for missing values in the intervention and control arms. From left to right imputed values increase in the intervention arm and reduce in the control arm. Imputed values are based on levels expected in each quantile of the study population. Change is presented as adjusted mean difference in diastolic blood pressure after 16 weeks moderate to high intensity exercise in mmHg with 95% confidence interval error bars

[figure not shown]

eFigure3. Sensitivity analysis using Multiple Imputation by Chained Equations (MICE) on the primary outcomes of 24hour awake ambulatory diastolic and systolic blood pressure. Change is presented as adjusted mean difference in each blood pressure variable between intervention and control groups after 16 weeks moderate to high intensity exercise in mmHg with 95% confidence interval error bars

[figure not shown]

eFigure 4. Forest plots to demonstrate the adjusted mean difference in awake systolic ambulatory blood pressure (Panel A) and awake ambulatory diastolic blood pressure (Panel B) after a 16 week moderate to high intensity exercise intervention compared to a control group according to different subgroups of the study population. Subgroups are based on defined values of baseline body mass index, glucose level, arterial stiffness and left ventricular mass (for those who underwent magnetic resonance imaging) Change is reported as the adjusted mean difference in mmHg with errors bars representing 95% confidence intervals. Abbreviations: BMI = body mass index, LV = left ventricular, SBP = systolic blood pressure, DBP = diastolic blood pressure.

PANEL A. Awake Systolic Ambulatory Blood Pressure

[figure not shown]

PANEL B. Awake Diastolic Ambulatory Blood Pressure

**
[figure not shown]
**

eFigure 5. Distributions of blood pressure within the study population before (left hand side) and after (right hand side) the 16 week moderate to high intensity exercise intervention. The distribution for the control and intervention arms are overlaid on each other within each graph. Abbreviation: BP=blood pressure

[figure not shown]

**5. TABLES**

| Quantiles | Systolic Blood Pressure |  | Diastolic Blood pressure |  |
| --- | --- | --- | --- | --- |
|  | Intervention | Control | Intervention | Control |
| 30 | 120 | 121 | 72 | 71 |
| 40 | 124 | 124 | 74 | 72 |
| 50 | 125 | 126 | 75 | 75 |
| 60 | 129 | 128 | 76 | 77 |
| 70 | 131 | 130 | 80 | 79 |

eTable 1. This table shows the values imputed for each quantile for both Systolic and Diastolic Blood Pressure for the first sensitivity analysis.

eTable 2. Sensitivity analysis using MICE

|  | Exercise Intervention | | Control | | Mean Difference (95%) | |
| --- | --- | --- | --- | --- | --- | --- |
|  | n | Mean (SD) | n | Mean (SD) | Unadjusted | Adjusted |
| **24 Hour Awake Ambulatory Systolic Blood Pressure** | | | | | |  |
| Baseline | 102 | 129.1 (9.3) | 101 | 128.3 (8.7) | - | - |
| 16 Weeks | 102 | 126.6 (11.3) | 101 | 126.0 (10.0) | 0.6 (0,1) | 0.0 (-2.6,2.7) |
| **24 Hour Awake Ambulatory Diastolic Blood Pressure** | | | | | |  |
| Baseline | 102 | 77.0 (6.4) | 101 | 77.4 (7.5) | - | - |
| 16 Weeks | 102 | 76.4 (6.9) | 101 | 75.6 (6.7) | - 1. (0,1) | 1. (-0.9,2.9) |

eTable 3. Per-protocol analysis

|  | Exercise Intervention | | Control | | Mean Difference (95%) | |
| --- | --- | --- | --- | --- | --- | --- |
|  | n | Mean (SD) | n | Mean (SD) | Unadjusted | Adjusted |
| **24 Hour Awake Ambulatory Systolic Blood Pressure** | | | | | | |
| Baseline | 82 | 129.41 (9.46) | 101 | 128.25 (8.68) | - | - |
| 16 Weeks | 71 | 126.93 (11.58) | 84 | 125.83 (10.00) | 1.10 | 0.02 (-2.87,2.92) |
| 52 Weeks | 63 | 127.81 (13.11) | 69 | 125.52 (11.82) | 2.30 | 1.52 (-1.61,4.65) |
| **24 Hour Awake Ambulatory Diastolic Blood Pressure** | | | | | | |
| Baseline | 82 | 77.48 (6.19) | 101 | 77.36 (7.46) | - | - |
| 16 Weeks | 71 | 76.51 (7.04) | 84 | 75.54 (6.73) | 0.97 | 0.61 (-1.41,2.64) |
| 52 Weeks | 63 | 77.01 (8.32) | 69 | 75.24 (7.76) | 1.77 | 1.31 (-0.88,3.49) |

eTable 4. Subgroup comparison of 24 Ambulatory Blood Pressure (mmHg) and Peak Oxygen Uptake (ml/kg/min) according to Volume of Weekly Supervised Exercise Completed.

|  | Exercise Intervention | | | Control | | Mean Difference (95%) | | | |
| --- | --- | --- | --- | --- | --- | --- | --- | --- | --- |
|  | n | Mean (SD) | | n | Mean (SD) |  | | | Adjusted |
| **24 Hour Awake Ambulatory Systolic Blood Pressure** | | | | | | | |  | |
| **Weekly Exercise Supervision ≥ 3 hours** | | | | | | | | | |
| Baseline | 45 | 129.6 (9.0) | | 101 | 128.3 (8.7) |  | | | |
| 16 Weeks | 43 | 127.7 (12.6) | | 84 | 125.8 (10.0) | -0.1 (-3.5,3.3) | | | |
| 52 Weeks | 35 | 129.2 (11.8) | | 69 | 125.5 (11.8) | 1.8 (-1.9,5.6) | | | |
| **Weekly Exercise Supervised < 3 hours** | | | | | | | | | |
| Baseline | 57 | | 128.8 (9.6) | 101 | 128.3 (8.7) | |  | | |
| 16 Weeks | 33 | | 125.9 (10) | 84 | 125.8 (10.0) | | 0.3 (-3.5, 4.1) | | |
| 52 Weeks | 33 | | 126.3 (14.8) | 69 | 125.5 (11.82) | | 1.3 (-2.7, 5.6) | | |
| **24 Hour Awake Ambulatory Diastolic Blood Pressure** | | | | | | | | | |
| **Weekly Exercise Supervision ≥ 3 hours** | | | | | | | | | |
| Baseline | 45 | | 77.4 (6) | 101 | 77.4 (7.5) | |  | | |
| 16 Weeks | 43 | | 77 (6.8) | 84 | 75.5 (6.7) | | 0.9 (-1.4,3.3) | | |
| 52 Weeks | 35 | | 78.3 (8.0) | 69 | 75.2 (7.8) | | 2.3 (-0.4,4.9) | | |
| **Weekly Exercise Supervision < 3 hours** | | | | | | | | | |
| Baseline | 57 | | 76.7 (6.7) | 101 | 77.4 (7.5) | |  | | |
| 16 Weeks | 33 | | 75.7 (7.2) | 84 | 75.5 (6.7) | | 0.3 (-2.4, 3.0) | | |
| 52 Weeks | 33 | | 75.2 (8.4) | 69 | 75.2 (7.8) | | 0.2 (-2.6, 4.9) | | |
|  |  | |  |  |  | |  | | |
| **Oxygen Uptake Peak** | | | | | | | | | |
| **Weekly Exercise Supervision ≥ 3 hours** | | | | | | | | | |
| Baseline | 45 | | 34.1 (7.8) | 100 | 34.7 (7.4) | |  | | |
| 16 Weeks | 45 | | 36.7 (7.6) | 92 | 34.6 (6.7) | | 3.0 (1.5, 4.5) | | |
| 52 Weeks | 41 | | 35.2 (8.3) | 81 | 34.5 (7.3) | | 0.7 (-0.9, 2.2) | | |
| **Weekly Exercise Supervision < 3 hours** | | | | | | | | | |
| Baseline | 56 | | 32.2 (6.6) | 100 | 34.7 (7.4) | |  | | |
| 16 Weeks | 39 | | 35.9 (6.2) | 92 | 34.6 (6.7) | | 2.4 (0.8, 3.9) | | |
| 52 Weeks | 36 | | 32.5 (6.2) | 81 | 34.5 (7.3) | | -0.6 (-2.2, 2.2) | | |
|  | | | | | | | |  | |

1. Protocol

**Study Title:**  Trial of Exercise to Prevent Hypertension in young Adults

**Internal Reference Number / Short title:** TEPHRA

**Ethics Ref:** 16/SC/0016 **IRAS Ref:** 194729

**Date and Version No:** 10th December 2020, Version 3.1

| **Chief Investigator:** | [name], PhD, FRCP  Professor of Cardiovascular Medicine and Consultant Cardiologist  Oxford Cardiovascular Clinical Research Facility  University of Oxford  Email: [contact]  [contact]  [contact] |
| --- | --- |

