The intention-to-treat analysis strategy used is a comprehensive examination of the conclusions drawn from the main analysis. For clarity, eTable 1 shows the values being imputed for each quantile for both Systolic and Diastolic Blood Pressure for the first sensitivity analysis.

In eFigure 1 and 2, we can see how the estimates of the adjusted mean difference change depending on the values we impute. As we use lower values to impute for the intervention arm and higher values in the control arm, the effect size creeps towards favouring the intervention, as one would expect. The opposite is also true, lower values in the control and higher values in the intervention makes the mean estimate trend towards favouring the control arm. When we impute the 70th quantile for the intervention and 30th quantile for the control we yield a statistically significant result favouring the control arm to a 5% significance level for both Systolic and Diastolic Blood Pressure.

This sensitivity analysis tells us that we would need to see a large violation of the MAR assumption assumed in the main analysis to render the results invalid and, given the reasons for missingness in the TEPHRA trial, this departure being a reality is unlikely.

For our second sensitivity analysis on missing data, we performed Multiple Imputation by Chained Equations (MICE). This method is widely used in research due to its ability to account for statistical uncertainty caused by the imputations by pooling multiple imputations and its flexibility to handle variables of varying types (binary or continuous). In our imputations, we have imputed using variables from our analysis model and not included other variables that may predict missingness. In this analysis we used 40 multiple imputations, analysed each “complete” dataset separately then pooled the results using the pool command from the mice package in R which averages the estimates of the complete data model, computes the total variance over the repeated analyses by Rubin’s rules (Rubin, D.B. (1987). Multiple Imputation for Nonresponse in Surveys. New York: John Wiley and Sons). Using 40 imputations minimises the error caused by the imputation process. We present the results as we did with the primary analysis - in eTable 2 and eFigure 3. As we have complete data for the primary outcome at baseline, no imputation was necessary and has been included in the eTable 2.

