#### 2. Per-Protocol Analysis

A sensitivity analysis on the primary outcome has been carried out on a per-protocol basis to examine robustness of conclusions to different assumptions about departures from randomised policies. The target intervention exposure was 3 aerobic sessions per week, completed on separate days, for 16 weeks, with a compliance threshold set at 80%; equivalent to ≥ 39 independent aerobic exposures with no greater than 2 weeks between exposures. Before recruitment commenced a compliant session was defined as a supervised exercise session, but during the course of the trial this definition was relaxed to include unsupervised sessions captured using the activity monitor. The same mixed model was used for the primary outcomes accounting for person random effects, baseline (as a continuous covariate) and 4-month blood pressure values (or peak oxygen uptake), gender, age (<24, 24–29, >30 years old), and gestational age (<32, 32-37, >37 weeks) as fixed effects with treatment by 16 week time point interaction also included was used to analyse 24 Hour Awake Ambulatory Blood Pressure (Systolic and Diastolic) on the per-protocol population. The results are presented in eTable 3, nonparametric 95% confidence intervals around the unadjusted mean difference and p-values are not presented. The results from the per-protocol analysis reinforce the interpretation of the main trial results: that there is no difference between the Control and Exercise Intervention groups in 24 Hour Awake Ambulatory Blood Pressure at 16 or 52 weeks post-randomisation.

3. Subgroup Analysis

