# STATISTICS AND ANALYSIS

## Description of Statistical Methods

The analysis will be carried out on the basis of intention-to-treat (ITT). This is, after randomisation, participants will be analysed according to their allocated intervention group irrespective of what they actually receive.

Patient demographic characteristics and other baseline information will be summarised by treatment group. Numbers (with percentages) for binary and categorical variables and mean (standard deviation), or median (interquartile or full range) for continuous variables will be presented. Normality of variables will be assessed by visual assessment of the normality curves and the Shapiro-Wilk test. The analysis of the primary outcome will be assessed using analysis of covariance (ANCOVA) adjusting for baseline values and minimisation factors used in the randomisation process. Results will be presented as adjusted mean difference in change in ambulatory blood pressure between randomised groups at 4 months with 95% confidence intervals (CI) and associated two-sided p value. The analysis of secondary outcomes will also be done using analysis of covariance (ANCOVA) to establish a co-variant model to examine the effect of cardiac structure, vascular function and lifestyle behaviours on exercise capacity. Outcomes measured on more than one occasion will be analysed using a mixed effects model. The data collected from the sub-study will be analysed using paired and independent T-test. If the model assumptions are not met and evidence of departure from Normality is observed, transformations of the data will be employed or non-parametric tests will be carried out. Statistical analysis will be carried out using STATA or SPSS statistical software.

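### Five intervals headed as 95% are wrong as printed: both unadjusted differences in eTable 2, and three 52-week rows in eTable 4

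*Supplement*

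**What the plan says.** The Supplement reports two-arm comparisons under a column headed "Mean Difference (95"%). Two tables matter here.

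- **eTable 2** reports the imputation analysis. Section 1 of the Supplement says of it "In this analysis we used 40 multiple imputations", with each completed dataset analysed separately and the results pooled by Rubin's rules. The systolic row at 16 weeks ends "0.6 (0,1) | 0.0 (-2.6,2.7"). The unadjusted diastolic cell also carries the interval (0,1), and the adjusted diastolic cell carries (-0.9,2.9).
- **eTable 4** reports adjusted differences by weekly exercise volume. Section 3 of the Supplement describes this analysis as post hoc and exploratory. The 52-week rows for under 3 hours read 1.3 (-2.7, 5.6) for systolic pressure, 0.2 (-2.6, 4.9) for diastolic pressure and -0.6 (-2.2, 2.2) for peak oxygen uptake.

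The protocol, under Description of Statistical Methods, asks for the adjusted mean difference "with 95% confidence intervals (CI) and associated two-sided p value". For eTables 2 and 4 the 95% label on the cells in question comes from the table headers.

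**The concern.** An interval from 0 to 1 mmHg around a difference of 0.6 looks like a precise estimate. It appears to exclude any reduction in blood pressure from exercise and any difference above 1 mmHg. About 101 people per arm with SDs of 10 to 11 cannot give that precision. The adjusted intervals in the same rows are about four to five times as wide.

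In eTable 4, inflated upper limits make the low-volume group at 52 weeks look compatible with larger values than the model supports. For peak oxygen uptake, the printed limit of 2.2 ml/kg/min leaves open a sustained gain that a limit near 1.0 would exclude.

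**Working it through.** **eTable 2: inputs.** Systolic at 16 weeks (n, mean, SD by arm): "102 | 126.6 (11.3) | 101 | 126.0 (10.0"). Diastolic: "102 | 76.4 (6.9) | 101 | 75.6 (6.7"). Printed interval in both rows: (0,1), half-width 0.5.

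**Unadjusted differences and standard errors**, with SE = sqrt(SD1²/n1 + SD2²/n2):
- Systolic: 126.6 - 126.0 = 0.6, which matches the printed estimate. SE = sqrt(11.3²/102 + 10.0²/101) = 1.497. 95% interval: 0.6 ± 1.96 × 1.497 = -2.33 to 3.53.
- Diastolic: 76.4 - 75.6 = 0.8. SE = sqrt(6.9²/102 + 6.7²/101) = 0.955. 95% interval: 0.8 ± 1.96 × 0.955 = -1.07 to 2.67.

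A pooled t interval gives -2.35 to 3.55 and -1.08 to 2.68. Over the rounding range of the inputs, the t limits stay within -2.47 to -2.24 and 3.44 to 3.67 (systolic), and within -1.20 to -0.97 and 2.57 to 2.80 (diastolic).

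These are minimum widths, because they treat imputed values as observed and Rubin's rules add between-imputation variance. As a rough guide, take the numbers observed at 16 weeks in eTable 4: 43 + 33 = 76 intervention and 84 control. With the same SDs, the SEs become 1.694 and 1.077, and the intervals -2.7 to 3.9 and -1.3 to 2.9.

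**Can (0,1) be rescued?**
- *Rounding to whole numbers.* The true limits could then lie no further apart than -0.5 to 1.5, a half-width of 1.0 at most. The minimum needed is 2.93 or 1.87.
- *A different confidence level.* A half-width of 0.5 centred on the estimate corresponds to about 26% confidence (systolic) and 40% (diastolic). At 95% it would need about 3,500 and 1,420 per arm.
- *Stacking the 40 datasets as one.* Dividing the SEs by sqrt(40) gives about 0.14 to 1.06 and 0.50 to 1.10, close to what is printed. This is a possible cause only. The Supplement describes proper pooling.

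**eTable 4: symmetry check.** A model-based interval is symmetric about its estimate. With one decimal printed, (upper - estimate) - (estimate - lower) can differ from zero by at most 0.05 + 0.05 + 2 × 0.05 = 0.2.

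| 52 weeks, under 3 h | Lower / upper half-width | Asymmetry | Upper limit in the row for 3 h or more | Mirrored upper limit |
|---|---|---|---|---|
| Systolic 1.3 (-2.7, 5.6) | 4.0 / 4.3 | 0.3 | 5.6 | 5.3 |
| Diastolic 0.2 (-2.6, 4.9) | 2.8 / 4.7 | 1.9 | 4.9 | 3.0 |
| Peak oxygen uptake -0.6 (-2.2, 2.2) | 1.6 / 2.8 | 1.2 | 2.2 | 1.0 |

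The other nine eTable 4 intervals, the two adjusted eTable 2 intervals and all four eTable 3 intervals are symmetric to within 0.1. In the three faulty rows the lower half-widths (4.0, 2.8, 1.6) fit the same group's 16-week half-widths: 3.8, 2.7 and 1.5 to 1.6. The upper half-widths do not fit for diastolic pressure or oxygen uptake. Together with three exact matches in three rows, this points to the upper limits as the wrong figures.

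**The case against.** **The unadjusted intervals are not a planned quantity.** This stands. The protocol asks for a 95% interval on the adjusted difference only. For the per-protocol table the Supplement says "nonparametric 95% confidence intervals around the unadjusted mean difference and p-values are not presented". The cells are nevertheless printed under a 95% header, so they have to be 95% intervals. A nonparametric method would not shrink the width to between a sixth and a quarter of what the SDs imply.

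**The diastolic sign.** A reader might infer that the diastolic estimate has the wrong sign and lies outside its own interval, because the cell reads as a hyphen followed by 1 with no decimal digit. The documents do not support that firmly. The adjusted cell beside it has also lost its decimal, the table uses hyphens for blank cells, and list numbering is visibly altered elsewhere in the text as read. The hyphen may be an extraction artefact. Read as +1, the estimate sits on the upper limit. The point does not need the sign.

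**The conclusion is untouched.** This also stands. The robustness statement rests on the adjusted column, eFigure 3 (adjusted differences only) and the quantile imputations. All three eTable 4 intervals include zero, as printed and as mirrored.

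**The two tables have different faults.** Agreed. eTable 2 shows a width that is impossible at 95%. eTable 4 looks like copied cells, and its systolic row is off by only 0.3 mmHg.

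**Conclusion.** Five printed intervals are wrong: two in eTable 2 and three in eTable 4. The unadjusted imputation intervals should be at least -2.3 to 3.5 (systolic) and -1.1 to 2.7 (diastolic) in place of 0 to 1. This rests only on the n, means and SDs in the same table.

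In eTable 4 the upper limits are overstated by about 0.3 mmHg, 1.9 mmHg and 1.2 ml/kg/min, on the assumption that the estimates and lower limits are right. The documents make that likely but cannot prove it. If both limits were right instead, the estimates would have to be about 1.45, 1.15 and 0.0.

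A reader might go further and take this as undermining the null result, or as casting doubt on every interval in these tables. Neither follows. The adjusted estimates are internally consistent, the overall conclusion does not change, and the remaining intervals pass the symmetry check. What needs correcting is false precision in the unadjusted imputation results and overstated upper limits in a post-hoc comparison.

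**What to change.** - Recompute the unadjusted column of eTable 2 from the 40 imputed datasets, with Rubin's-rules 95% intervals to one decimal.
- Check the printed unadjusted diastolic estimate against the arm means, which give +0.8.
- Re-export the three 52-week intervals for under 3 hours in eTable 4 directly from the fitted model. Do not mirror the lower limits.
- Before reissue, check every adjusted interval for symmetry and every unadjusted interval against its n and SD.

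The cost is rerunning the output for two tables. Design, data and planned analyses stay as they are.
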